# Aim of the protocol

This protocol shall serve as an internal memorandum on methods and procedures of the Door-to-Door versus Pitso-study to be held from October to December 2011 within the project area of the SolidarMed project SMART III in Lesotho. It is based on the proposal submitted to the National Ethics Committee but elaborates more in detail the operating procedures. It is addressed to all staff – either at headquarters SolidarMed in Switzerland or in the field in Lesotho in order to ensure a common understanding of the study and consistency in study-procedures.

# Explanation of abbreviations and terms:

**HTC:** HIV Testing and Counselling

**ART:** Antiretroviral Treatment

**Pitso**: Traditional way of community gathering to promote health services. In the case of promotion of HTC, the community is mobilized through village-authorities (chief) a few days prior and then gathers near the chief’s place. After a general health education to all people attending, services are provided within two tents (mobile clinic) that ensure confidentiality.

**Door-to-door**: After having been sensitized through village-authorities a few days ago (same way of sensitization as for pitso), health care workers visit the people’s homes where they propose the services (“home-based testing”).

# Study-Methods

## AIM OF THE STUDY

To compare door-to-door versus pitso in delivering HTC within an integrated package in rural Lesotho in terms of people newly tested positive for HIV and enrolled into chronic HIV-care.

## Hypothesis

In comparison to the traditional “Pitso”-approach (community gathering), the door-to-door approach will result in a higher uptake of HTC, more newly detected HIV-positive persons and more patients newly enrolled into chronic HIV/AIDS-care using the same resources (financial, time and HR). The effect will be measurable as a a higher proportion and absolute number of people being tested HIV-positive, and on a cluster-level (health center) by a higher number of people enrolled in chronic HIV/AIDS care during the month following the campaigns.

## OBJECTIVES OF THE STUDY

1. Main objective
   1. To compare door-to-door versus pitso in terms of:
      1. HTC-uptake
      2. Newly tested HIV-positive persons
      3. Enrollment into chronic HIV/AIDS care (pre-ART or ART) among newly tested HIV-positive persons
2. Secondary objectives
   1. To compare door-to-door versus pitso in terms of
      1. Proportion of first-time testers
      2. Patient-characteristics (age, sex, first-time tester)
      3. Average CD4-count among clients newly tested HIV-positive
      4. Clinical WHO-stage among clients newly tested HIV-positive
      5. Uptake of other services provided
         1. Blood-pressure measurement
         2. Blood-glucose measurement
         3. Family Planning
         4. Immunization
         5. Deworming
         6. Vitamin A
      6. Detection of Tuberculosis suspects
      7. Sputum turn-around of Tuberculosis suspects
      8. Sputum-results of Tuberculosis suspects
   2. To assess among the clients participating in the study the rate of:
      1. High Random Glucose
      2. High Blood Pressure
      3. Undernutrition/Obesity

## STUDY DESIGN

Prospective cluster-randomized study. Each health center within the SMART project area (n=12) with its catchment area represents a cluster. One study arm provides integrated HTC using the door-to-door approach (6 HCs) as compared to the other arm using the pitso-approach (6 HCs)

## STUDY SETTING

The study will take place within the catchment areas of Seboche and Paray Mission hospital. Both hospitals belong to the Christian Health Association of Lesotho (CHAL). Seboche hospital is situated in the northern Lesotho, district Butha Buthe, has an estimated population of about 55’000 and an estimated adult HIV-prevalence of 16%. Paray Mission hospital is situated in the central district Thaba Tseka with an estimated catchment population of 77’000 and an estimated HIV-prevalence of 20%. Routine ART and HTC services are offered at the hospitals and at the health centres belonging to the catchment areas (5 health centres in Seboche hospital and 7 in Paray hospital catchment area). Under the supervision of the professional and senior counselor, lay-counsellors perform HTC at hospital as well as health center level. The catchment populations of health centers vary between 4’000 and 10’000 in 20 to 60 main-villages that are sometimes again divided into up to 5 sub-villages.

## INTERVENTIONS

### Campaigns

In both study-arms campaigns promoting HTC within an integrated package of primary health care services are held. One study arm promotes the package using the pitso approach whereas the other arm applies the door-to-door approach. The mobilization of the community is done 4 to 7 days prior to the campaign using the same means (village authorities) in both approaches. For both approaches mobilization is done through a letter to the village chief where the activity and the date are announced. The village chief has then the responsibility to inform the community (this is an often applied approach and all village chiefs are used to this procedure). Teams consisting of 2 nurses, 2 lay-counselors and one study-supervisor, will perform the campaigns for the integrated package. The campaigns are held during five days, Monday to friday (each day another village) in 5 selected villages in the catchment area of each of the 12 health centers. If there are enough human resources at the health center, 1 nurse and 1 lay-counselor will be delegated from the health center, the other nurse and lay-counsellor are from the primary health care team of the hospitals (Seboche or Paray) in order to ensure consistency in procedures. In case of shortage at health center level, the whole team will be delegated from the hospital.

In both kind of campaigns exactly the same service package is provided. It consists of:

1. HIV counseling and testing
2. Blood Sugar testing
3. Blood Pressure measurement
4. Tuberculosis screening
5. Immunization for eligible children and women
6. Vitamin A for eligible children and women
7. Deworming for eligible children
8. Family planning for eligible women
9. Health Education focusing on HIV/AIDS and TB for all

### Procedures

The procedures are defined in the Standard of Procedures (SOP) manual (see annex 1). Study-team-members have been instructed on the SOPs and conducted 4 pre-test campaigns under supervision. The pre-test villages belong to catchment areas that are not part of the study.

In case the team encounters severely ill clients with danger signs, the patients will be transported in the study-car to the hospital (Seboche or Paray hospital), see annex 1.

### Intervention 1: Community gathering HTC

In case of intervention 1, the integrated package will be delivered through community gatherings (pitso). After mobilization through village authorities, the community will be sensitized in health talks and subsequently invited to get the integrated package in one of two tents that ensure confidentiality.

### Intervention 2: Door-to-door HTC

In case of intervention 2, the integrated package will be proposed at home. After information of the community via village authorities, two teams (each consisting of one lay-counselor and one nurse) will visit the people’s homes and propose the integrated package to the families.

## Randomization and allocation

### Clusters and sub-clusters

One Health Center with its catchment area forms a cluster. There are 12 Health Centers participating in the study, resulting in 6 Clusters per arm. The interventions (HTC-campains) will be held in 5 sub-clusters (villages) each.

### Randomization

The 12 health centers were openly randomized into two equal groups. Before randomization, clusters were stratified and paired according to their average-numbers of monthly new HIV-positive tested clients at routine clinic-based HTC (routine data from October to December 2010).

During an official meeting held on October the 3rd, a person not involved in the study threw a coin for one health center in each pair to allocate it either to the door-to-door or the pitso-arm. The other health center in the pair then automatically fell into the other arm. Table 1 shows the cluster-pairs and their allocation:

| **Pitso-arm** | **Door-to-Door arm** | **Time-frame of campaign** |
| --- | --- | --- |
| St Theresa HC (Paray) | St Peters HC (Seboche) | 17.-21. October 2011 |
| Ngoajane HC (Seboche) | Sehong Hong HC (Paray) | 24.-28. October 2011 |
| Linakeng HC (Paray) | Mokoto HC (Paray) | 31.10.-4.11. 2011 |
| Muela HC (Seboche) | Mohlanapeng HC (Paray) | 7.-12. November 2011 |
| Katse HC (Paray) | Boiketsiso HC (Seboche) | 14.-18. November 2011 |
| Khohlonso HC (Seboche) | Makhunoane HC (Seboche) | 21.-25. November 2011 |

Table 1 Matched pairs of clusters (health centers), their allocation to the study-arms and period where campaigns are held.

## Conduction of campaigns

Per cluster, campaigns are held during 5 days (Monday to Friday), each day in another village (subcluster) within the catchment area of the health center. Depending on the allocation of the cluster, either 5 days of door-to-door or 5 days of pitso campaigns are held. Both kinds of campaigns receive the same human and time-resources: 2 nurses, 2 lay-counsellors and one study-supervisor; timeframe: campaigns start at 9 am and end at 5 pm. A matched cluster-pair holds their campaigns at the same time (one pitso, the other door-to-door).

## Eligibility criteria

### Clusters

All Health Centers (12) within the SolidarMed SMART project area are eligible

### Sub-clusters (villages)

Villages are eligible if:

- clearly confined to the catchment area of the health center (not on border between two catchment areas
- Population of at least 25 households
- Distance to health center 3 to 20km

### Individuals

Individuals are eligible if:

- resident in the catchment area of the health center where the campaign is conducted
- Provision of written informed consent to participate (signed by writing or fingerprint) (see annex)
- In case of children (<16yrs): Provision of informed written consent by care-taker (signed by writing or fingerprint)
- Clients refusing consent for HTC but providing consent to participate in the study are still eligible

Eligibility for HTC:

- Eligibility for HTC follows the national HTC guidelines. All clients with an unknown HIV-status and who did not test negative within the previous 3 months, who are ≥ 12 years or are in company of an adult (≥18 years) care-taker who provides consent, are eligible. For HTC the client or his/her care-taker must provide written informed consent on the national HTC-consent form. In case of children below < 18 months, HTC is still offered as recommended in the national guidelines. However, in case of a positive test-result, referral to health center for PCR-testing is done.

Individuals who are not eligible for the study are nevertheless offered the same service-package.

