### Individuals

Individuals are excluded from the study if:

- Not fulfilling eligibility criteria

In addition individuals are excluded for the analysis of the primary outcomes if:

- Already known HIV-positive
- Prior HIV-test < 3 months (window-period)

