**Selection of individuals:**

- Door-to-Door: All members of a household (irrespective of age) will be proposed the integrated package including HTC.
- Pitso approach: All persons attending the pitso will be invited to receive the integrated package

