## Outcomes measured

### Sources of outcomes

Sources of the different outcomes measured are the study-questionnaire (see annex 2), and the following official registers at the health centers: HTC-register, pre-ART register, ART-register, tuberculosis-suspect register

| *Outcome variable* | *Hypothesis* | *Source/Measure* | *Statistical Method* |
| --- | --- | --- | --- |
| **Primary outcomes** |  |  |  |
| 1. Proportion and absolute number of clients accepting HTC | Higher in door-to-door | Source: study-questionnaire | logistic regression |
| 1. Proportion and absolute number newly tested HIV-positive | Higher in door-to-door | Source: HIV-test result from Determine® & Double Check® (according national guidelines) [binary/count] | logistic regression |
| 1. Proportion and absolute number newly enrolled on chronic HIV/AIDS care within one month after the campaign of those newly tested during campaign | Higher in door-to-door | Source: study-questionnaire and pre-ART and ART-Registers. Enrolled (Y/N) [binary/count] | logistic regression |

| **Secondary outcomes** |  |  |  |
| --- | --- | --- | --- |
| 1. Proportion of first-time testers | Higher in door-to-door | Study-questionnaire [binary] | logistic regression |
| 1. Age of clients attending HTC | Lower in door-to-door | Study-questionnaire [cont] | t-test/ranksum test |
| 1. Sex of clients attending HTC | Proportion of male testers is higher in door-to-door | Study-questionnaire [binary] | logistic regression |
| 1. Proportion newly tested HIV-positive with advanced disease (WHO-stage 3 or 4) | - | Study-questionnaire [binary] | logistic regression |
| 1. Average CD4-count of clients newly tested HIV-positive | - | On-site CD4-count using PIMA^TM^ [cont] | t-test/ranksum-test |
| 1. Absolute number and proportion of clients screened positive for tuberculosis | - | Study-questionnaire [count/binary] | logistic regression |
| 1. Absolute number and proportion of clients positively screened for tuberculosis who bring their sputum to the facility within ≤ 5 days | - | Study-questionnaire and tuberculosis-suspect register | logistic regression |
| 1. Absolute number and proportion of clients bringing their sputum bottles who have a positive direct sputum smear | - | Study-questionnaire and tuberculosis-suspect register | logistic regression |
|  |  |  |  |

Table 2 Primary and secondary outcomes measured in the study

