# Annex 1: Standards of procedures

**Standard Operation Procedures for HTC-campaigns**

- fill-in a file for each client approached for the provision of services
- follow the order of services provided as outlined below

| **Number** | Consecutive numbering. Each team starts every day at 1 |
| --- | --- |
| **Name** | Write Full Name |
| **Resident in CA?** | If the client is resident in the catchment area of the health center where the campaign takes place 🡪 tick Yes |
| **Blood Pressure** | Provide this service to all patients >18 years and write measured blood-pressure into the case. For children 🡪 leave empty.  If blood-pressure ≥140/90 mmHg 🡪 refer to health center for follow-up |
| **HTC accepted** | Propose HTC to all clients (independent of age) who are not already confirmed HIV-positive. All clients agreeing to HTC must fill out the national HTC-consent form!   - if client accepts HTC 🡪 tick “Yes” - if client does not accept HTC 🡪 tick “No” - if client states to be HIV-positive 🡪 tick “ICDP” - if it is a child < 12 years without her/his care-taker 🡪 tick “no guard” - if client is currently in the window-period (<3months since last HIV-test, as confirmed in bukana) 🡪 tick “window”   In case of children < 18 months with a positive HIV-antibody test, the care-taker must be counselled to seek care at the health center for a PCR-confirmation test. |
| **1^st^ time tester** | - if client states that he has never tested before 🡪 tick “Yes” - if client states that he once tested before 🡪 tick “No” - if client is not tested for any reason 🡪 tick “NA” |
| **Test result** | Copy result from test: Positive or Negative or Indeterminate  If the test is positive, the national HTC referral form must be filled out. A list of all newly patients tested positive must be provided to the health center. Patients who do not appear at the health center within 1 month must be traced by the health center (using the SolidarMed tracing fund) |
| **WHO-stage** | Stage all clients with a positive HIV-test according to WHO-staging (see annex) |
| **CD4-count** | Perform CD4-count (PIMA) to all clients who test HIV-positive and note the count in the field. |
| **Height/Weight** | Put height in cm and weight in kg |

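### Children under 18 months with an unconfirmed positive antibody test count as newly HIV-positive in the second primary outcome and enter the base of the third

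*Protocol*

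**What the plan says.** Under Eligibility criteria, Individuals, the protocol states: "In case of children below < 18 months, HTC is still offered as recommended in the national guidelines". It then adds: "However, in case of a positive test-result, referral to health center for PCR-testing is done". Annex 1, in the row on accepting HTC, repeats the rule. "In case of children < 18 months with a positive HIV-antibody test", it says, "the care-taker must be counselled to seek care at the health center for a PCR-confirmation test". The protocol therefore regards the rapid result at this age as needing confirmation.

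Table 2 (Outcomes measured) defines the second primary outcome as "Proportion and absolute number newly tested HIV-positive", with the source given as "HIV-test result from Determine® & Double Check® (according national guidelines". It sets no age limit. The third primary outcome is enrolment in chronic HIV care within one month among those found positive at the campaign.

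Exclusion criteria, Individuals, has a list introduced by "In addition individuals are excluded for the analysis of the primary outcomes if". It holds two items: HIV status already known to be positive, and a test within the last three months. Age is not among them.

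The campaign form (Annex 2) has one test result with three options. Neither the variables collected at the campaign nor those collected at five weeks include a PCR result, and the outcome section of the form has no field for one.

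**The concern.** Two of the three primary outcomes rest on a case definition that the protocol itself does not accept as final for one age group. An infant who is antibody-positive but not infected is counted as a newly detected case. The same infant joins the list of positives whose enrolment is looked up in the registers. If PCR is negative, the infant has no reason to enrol and is scored as a failure of linkage, although the referral worked. Because no PCR result is gathered, these children cannot be reclassified afterwards from the planned data.

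The yield of each approach would be overstated and its linkage understated. If one approach tests relatively more infants, part of the difference between arms would come from the case definition and not from the approach.

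**Working it through.** **The plan's own figure.** The only sample size is for outcome 1, HTC uptake. Inputs from Sample size: 80% against 65%, k = 0.1, 200 clients per cluster, 80% power, 5% significance (taken as two-sided). With the unmatched Hayes and Bennett formula:

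c = 1 + (1.96 + 0.84)² × [0.65×0.35/200 + 0.80×0.20/200 + 0.1²×(0.65² + 0.80²)] / 0.15²
= 1 + 7.85 × 0.01256 / 0.0225 = 5.38, rounded up to 6.

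The stated 6 per arm reproduces. It concerns uptake and does not depend on how infants are classified.

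**What follows from the text.** Infants are tested; a positive rapid result is recorded as positive; outcome 2 reads that result; no exclusion removes the child; no PCR result replaces it. No single sentence says that infants count as cases, but no step in the plan takes them out.

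**Illustration of size.** From the protocol: 6 × 200 = 1,200 attendees per arm, so 960 tested in door-to-door (80%) and 780 in pitso (65%). Study setting gives HIV prevalence of 16% and 20%, used here as a proxy for the antibody-positive share *a* among infants. Everything else is assumed:

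- infant share of testers *s*: 2% or 5% in both arms; or unequal, as 2% pitso against 5% or 8% door-to-door, or 5% against 10%;
- truly infected share of antibody-positive infants *t*: 5% or 30%;
- positivity in all other testers *y*: 3%, 5% or 10%, equal in both arms;
- 50% of truly infected clients enrol, and PCR-negative infants never do;
- the proportion in outcome 2 is taken among those tested.

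Formulas:

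- recorded positive proportion = (1−s)y + s·a
- false positives among testers = s·a·(1−t)
- observed enrolment = 0.5 × (1 − false positives / recorded positives)

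Worked case with equal shares (s = 5%, a = 20%, t = 5%, y = 5%):

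- recorded positives: 0.95×0.05 + 0.05×0.20 = 0.0575
- false positives: 0.05×0.20×0.95 = 0.0095, which is 16.5% of recorded positives
- in numbers: 780 × 0.0095 = 7.4 in pitso and 960 × 0.0095 = 9.1 in door-to-door
- observed enrolment: 0.5 × (1 − 0.165) = 41.7% in both arms, against an assumed true 50%
- odds ratio between arms: 1.00 for both outcomes

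The same case with 10% infants in door-to-door and 5% in pitso:

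- door-to-door recorded positives: 0.90×0.05 + 0.10×0.20 = 0.065
- outcome 2 odds ratio: (0.065/0.935) / (0.0575/0.9425) = 1.14
- door-to-door enrolment: 0.5 × (1 − 0.019/0.065) = 35.4%
- outcome 3 odds ratio: (0.354/0.646) / (0.417/0.583), which is 0.76 before rounding

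Across the grid:

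| Infant shares | False among recorded positives | Odds ratio, outcome 2 | Odds ratio, outcome 3 |
|---|---|---|---|
| Equal in both arms | 2% to 25% | 1.00 | 1.00 |
| Higher in door-to-door | up to 25% pitso, up to 40% door-to-door | 1.02 to 1.32 | 0.61 to 0.94 |

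Odds ratios compare door-to-door with pitso. With *y* equal in both arms, restricting to 18 months or more returns an outcome 2 odds ratio of 1.00 in every row.

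**The case against.** **Both arms test all ages.** Door-to-door teams follow the rule "All members of a household (irrespective of age) will be proposed the integrated package including HTC", but everyone attending a pitso is invited too, and the child services on offer in both arms could draw infants to either. A reader might infer that the definition biases the two arms differently. The documents do not support that as a fact. Table 2 expects younger clients in door-to-door, but that is a hypothesis about age overall, which more adolescents or young adults would also satisfy. No infant numbers are given. This part of the objection stands.

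**Enrolment pending PCR.** A reader might also infer that antibody-positive infants wait for PCR and so miss the one-month window. No section says so. Under Annex 1 the health center receives the list of positives and traces those who do not come. Whether an infant may be enrolled before PCR depends on national guidelines that are not at hand. Only PCR-negative infants who do not enrol lower outcome 3, and their share is unknown. This also stands.

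**Not every antibody-positive infant is an error.** Some are infected, so treating all of them as false would overstate the problem. This is why *t* appears in the calculation.

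**The guidelines or the analysis plan may settle it.** Table 2 refers to national guidelines, age is recorded, and a statistical analysis plan that is not shown could set an age limit. That is possible. But the protocol names only the two rapid tests and fixes its own list of primary-analysis exclusions, and an analysis plan cannot restore PCR results that nobody was asked to collect.

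**Conclusion.** The case definition is inconsistent with the protocol's own confirmation rule, and the inconsistency reaches outcomes 2 and 3. Reported new positives are inflated in both arms, in number and proportion. The enrolment proportion is lowered to the extent that PCR-negative infants do not enrol.

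For the comparison of arms the conclusion is conditional. Equal infant shares create no spurious difference in proportions; if the true yields differ, they dilute the ratio towards 1. The absolute counts, which the protocol also compares, would still gain more in door-to-door because more people are expected to be tested there (9.1 against 7.4 in the worked case). If door-to-door tests relatively more infants, outcome 2 shifts in its favour and outcome 3 against it.

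The size cannot be derived from the documents. The ranges above rest on assumed infant shares, infection rates, yields and enrolment, with the stated prevalence as a proxy. Outcome 1 and its sample size are unaffected. The point should be corrected because two primary outcomes are involved and the change is small.

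**What to change.** In Exclusion criteria, Individuals, add to the primary-analysis exclusions that outcomes 2 and 3 are restricted to clients aged 18 months or more. Apply the same limit to the CD4 and WHO-stage summaries, which describe the same new positives. Report antibody-positive children under 18 months separately by arm, and add a sensitivity analysis that includes them in outcomes 2 and 3.

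The form in Annex 2 has an age field without a unit, so it should ask for months in young children; otherwise the limit cannot be applied reliably.

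Reporting PCR-confirmed infants is optional. It would need a PCR field in the five-week register check, which is extra data collection.

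The cost is an added exclusion line, a unit on the form and a separate tabulation. A few recorded positives leave the primary analysis: on the assumptions above, 780×0.02×0.16 = 2.5 to 780×0.05×0.20 = 7.8 in pitso, and 960×0.02×0.16 = 3.1 to 960×0.10×0.20 = 19.2 in door-to-door. Some of these are truly infected infants, at most 30% of them under those assumptions, and the separate report keeps them visible. Testing and referral of infants and the number of clusters stay as they are.
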